# The Smart City Active Mobile Phone Intervention (SCAMPI) study to promote physical activity through active transportation in healthy adults: a study protocol for a randomised controlled trial

**DOI:** 10.1186/s12889-018-5658-4

**Published:** 2018-07-16

**Keywords:** Accelerometer, Active transport, Application, Behaviour change, mHealth, Smartphone, Physical activity, Walkability

## Abstract

**Background:**

The global pandemic of physical inactivity represents a considerable public health challenge. Active transportation (i.e., walking or cycling for transport) can contribute to greater total physical activity levels. Mobile phone-based programs can promote behaviour change, but no study has evaluated whether such a program can promote active transportation in adults. This study protocol presents the design and methodology of The Smart City Active Mobile Phone Intervention (SCAMPI), a randomised controlled trial to promote active transportation via a smartphone application (app) with the aim to increase physical activity.

**Methods/design:**

A two-arm parallel randomised controlled trial will be conducted in Stockholm County, Sweden. Two hundred fifty adults aged 20–65 years will be randomised to either monitoring of active transport via the TRavelVU app (control), or to a 3-month evidence-based behaviour change program to promote active transport and monitoring of active travel via the TRavelVU Plus app (intervention). The primary outcome is moderate-to-vigorous intensity physical activity (MVPA in minutes/day) (ActiGraph wGT3x-BT) measured post intervention. Secondary outcomes include: time spent in active transportation measured via the TRavelVU app, perceptions about active transportation (the Transport and Physical Activity Questionnaire (TPAQ)) and health related quality of life (RAND-36). Assessments are conducted at baseline, after the completed intervention (after 3 months) and 6 months post randomisation.

**Discussion:**

SCAMPI will determine the effectiveness of a smartphone app to promote active transportation and physical activity in an adult population. If effective, the app has potential to be a low-cost intervention that can be delivered at scale.

**Trial registration:**

ClinicalTrials.gov NCT03086837; 22 March, 2017.

## Background

Promoting physical activity is considered the best buy in public health [1]. The health benefits of regular physical activity are considerable [2–4] and occur even with modest improvements in activity levels [5]. Despite these benefits, 31% of the global population are physically inactive [6], therefore, low-cost interventions that can be delivered at scale are a public health priority [7]. One way to increase physical activity at the population level is to make it easier to integrate in individuals’ daily life routines [8]. Active transportation (i.e., any self-propelled mode of transportation to get from one place to another such as walking or biking to work, school, or running errands) has been shown to be a feasible approach (i.e., more convenient and affordable in comparison with planned exercise/recreational activity) for increasing total physical activity levels [9]. Thus, active transportation is an optimal target for physical activity promotion with substantial health benefits at a population level [10–12]. For instance, active transportation has been inversely associated with all-cause mortality, cardiovascular disease, falls, impaired mental health, type 2 diabetes and obesity [12–14]. Cycling or walking to work was associated with a 50% lower risk for type 2 diabetes when compared to car, taxi or motorcycle transportation [14]. Furthermore, walking or cycling for transportation was associated with a lower body mass index (BMI) when compared to those who went by car, taxi or motorcycle [13].

The ubiquitous use of smartphones offers considerable possibilities for the promotion of physical activity, particularly active transportation. In-built (native) sensors in smartphones, such as accelerometers, gyroscopes and global positioning systems (GPS) can be used to track people’s travel modes (e.g., walking, cycling, and motorised transportation) and provide information such as speed, duration and length of travel behaviour. Mobile health (mHealth, including smartphones), interventions are possible to deliver at scale, and have a number of benefits over traditional intervention approaches. mHealth programs can be delivered anywhere at any time, are interactive, and can be tailored to meet people’s needs. Compared to traditional face-to-face counselling such programs are less time-consuming and cheaper to deliver [15]. Recent systematic reviews have concluded that mHealth programs may be useful for achieving changes in behaviour such as physical activity, and for weight loss [16–18]. In the context of active transportation, smartphones can be used to provide real-time measures of travel behaviour and deliver a behaviour change intervention. One previous study used a smartphone app to promote active transport at a university campus; however, it was part of a multi-strategy campaign, thus, the effect of the app itself could not be evaluated [19, 20]. To the best of our knowledge no study has evaluated whether a smartphone application (app) can promote active transportation.

### Aims

The aim of this paper is to report the study design and methodology of the Smart City Active Mobile Phone Intervention (SCAMPI). The primary aim of SCAMPI is to examine if an app can promote active transportation to increase physical activity in adults. Secondary aims are to determine the effects of SCAMPI on active transportation, attitudes towards active transport and health related quality of life.

### Hypothesis

The primary hypotheses are that compared to controls, the intervention group will spend more time (minutes per day) on moderate-to-vigorous intensity physical activity (MVPA) immediately post-intervention and at the 6 month follow-up. Secondary hypotheses are that the intervention group will spend more time on active transportation (cycling or walking), that the intervention effect will be larger among those who at baseline perceive their neighbourhood walkability as low and that attitudes towards active transport will improve more compared to the controls. We further hypothesize that the intervention group will report improved health related quality of life at the end of the intervention and at the 6 month follow-up.

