### Outcomes and measures

The primary outcome is MVPA post intervention (i.e., 3 months post randomisation). Secondary outcomes include active transportation, neighbourhood walkability, health related quality of life and attitudes towards active transportation. Outcomes are assessed at baseline and at 3 and 6 months post randomisation. See Table 2 for an overview of all assessments. Unexpected and adverse events are voluntarily reported by participants to the research team and will be reported.

**Table 2 Tab2:** Outcomes and other measures collected at the different time points

		Baseline	3 months	6 months
*Assessments*	*Measure*			
MVPA, minutes/day	ActiGraph wGT3x-BT	x	x	x
Leisure and work time physical activity^a^	Questionnaire	x	x	x
Travel behaviour (active transportation)	Smartphone application (TRavelVU)	x	x	x
Health related quality of life	RAND-36	x	x	x
Attitudes towards active transportation	Transport and physical activity questionnaire (TPAQ)	x	x	x
Neighbourhood walkability	Neighbourhood environment walkability scale (NEWS)	x		
Sociodemographic factors^b^	Questionnaire	x		

Abbreviations: *MVPA* moderate-to-vigorous physical activity

^a^Two questions in the web-based questionnaire are used to assess leisure and work time physical activity [34]

^b^Occupational status, area of residency, type of housing and access to a bicycle were also repeated at the 3 and 6 month follow-ups

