### Statistical analyses

Trial evaluation will be performed with linear mixed model analyses using intention to treat principles. In the statistical models we will use time as a categorical variable (0, 3 and 6 months) with time 0 as a reference group and include an interaction between group and time. The dependent variable is post intervention scores for MVPA (i.e., minutes/day) and the secondary outcomes (e.g., active transportation (minutes/day)). Three-way interactions will be analysed in order to evaluate if the intervention effect was moderated by any of the baseline covariates (e.g., age, sex, educational attainment, neighbourhood walkability or health related quality of life). Missing values on baseline covariates and on follow-up assessments will be imputed simultaneously using multiple imputation with chained equations [m (number of imputations) = 20] [44] taking into account variables of importance for predicting the missing values (e.g., age, sex, country of birth, educational attainment, occupation, season for intervention (i.e., autumn or spring) etc.). Continuous variables will be imputed using predictive mean matching (5 nearest neighbours). Binary variables will be imputed using logistic regression, and multi-categorical variables will be imputed using ordinal logistic regression (if ordered) or multinomial logistic regression (if unordered). Descriptive data over adherence to the intervention will be presented. Per protocol analyses examining effects related to adherence to the intervention (e.g., number of registered days in the app, goals set and achieved) will be conducted using linear mixed models adjusting for age, sex, country of birth (Sweden/not Sweden), educational attainment, occupation and season for intervention. As in the primary analysis, time, group and time-group-interactions will also be included. Sensitivity analyses concerning deviations from the missing at random assumption will be performed using delta-adjustment [45]. Statistics Sweden will provide summary statistics for responders and non-responders regarding age, sex, country of birth, education level and area of residence. All *p*-values < 0.05 (two-sided) will be regarded as statistically significant.

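### MVPA at 6 months is a primary hypothesis in one section and has no outcome status elsewhere, so the plan does not settle which result confirms the trial

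*Protocol article*

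**What the plan says.** Five places in the protocol article bear on this point.

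- **Hypothesis.** The primary hypotheses, in the plural, set the two arms against each other: "the intervention group will spend more time (minutes per day) on moderate-to-vigorous intensity physical activity (MVPA) immediately post-intervention and at the 6 month follow-up".
- **Abstract, Methods/design.** One primary outcome is given: "The primary outcome is moderate-to-vigorous intensity physical activity (MVPA in minutes/day) (ActiGraph wGT3x-BT) measured post intervention".
- **Outcomes and measures.** The time point is made explicit: "The primary outcome is MVPA post intervention (i.e., 3 months post randomisation". The next sentence reads "Secondary outcomes include active transportation, neighbourhood walkability, health related quality of life and attitudes towards active transportation". MVPA at 6 months is not in that list, although Table 2 shows it is measured.
- **Sample size and power considerations.** One comparison is powered: a 10-minute difference, SD 25 minutes, alpha 0.05, 80% power, 100 completers per arm, 250 enrolled.
- **Statistical analyses.** The mixed model takes "time as a categorical variable (0, 3 and 6 months) with time 0 as a reference group and include an interaction between group and time", so it yields a group contrast at 3 months and another at 6 months. The section closes with "All *p*-values < 0.05 (two-sided) will be regarded as statistically significant" and puts neither time point ahead of the other.

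**The concern.** A reader who wants to know what result would confirm the trial gets two answers. By the Outcomes section it is the 3-month difference. By the Hypothesis section the 6-month difference is primary as well, and that is the only status the article gives it.

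The two contrasts answer different questions. The behaviour change features of the app disappear after 3 months (Intervention, Overall), so the first contrast measures the effect at the end of the programme and the second measures what persists without it. They could well disagree. If the 3-month test missed and the 6-month test fell below 0.05, the Hypothesis section together with the flat significance rule would let the authors report a confirmed primary hypothesis. The Outcomes section would call the same trial negative on its primary outcome. The stated 5% error and 80% power both hold under only one of the possible readings.

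**Working it through.** **Inputs from the article.** Difference 10 min/day, SD 25 min, two-sided alpha 0.05, power 80%, 100 completers per arm, drop-out 20%, 250 enrolled (Sample size and power considerations; sidedness from Statistical analyses).

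**Inputs assumed.** The correlation rho between the 3- and 6-month test statistics is not given, so a range is shown. Where both time points must succeed, a true difference of 10 minutes at each is assumed.

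**Step 1: reproduce the stated size.**
n per arm = 2 × (1.960 + 0.842)² × 25² / 10² = 98.1, rounded up to 99, or 198 in total against 200 stated.
With 100 per arm the standard error is 25 × √(2/100) = 3.54 and the expected z is 10 / 3.54 = 2.83. Power = Φ(2.83 − 1.96) = 80.7% (80.4% with the noncentral t).
Enrolment = 200 / 0.80 = 250.
The stated figures are right for **one** test at the full 0.05.

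**Step 2: the three readings.**

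*(a) Only 3 months is primary.* Error 5%, power about 80%. Everything stands.

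*(b) Either time point suffices.* Two-sided error = 1 − P(|Z1| < 1.96, |Z2| < 1.96), bivariate normal. Error in the hypothesised direction = 1 − P(Z1 < 1.96, Z2 < 1.96).

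| rho (assumed) | Two-sided error | Favouring the intervention |
|---|---|---|
| 0 | 9.75% | 4.94% |
| 0.3 | 9.51% | 4.76% |
| 0.5 | 9.07% | 4.54% |
| 0.7 | 8.35% | 4.17% |
| 0.8 | 7.81% | 3.90% |
| 0.9 | 7.04% | 3.52% |

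The ceiling is 1 − 0.95² = 9.75%. The two-sided error tends to 5% as rho tends to 1. The single-test references are 5% and 2.5%.

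*(c) Both time points are required.* Error is at most 5%. Power = P(Z1 > 1.96, Z2 > 1.96) with both means at 2.83:

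| rho (assumed) | Power, 100 per arm |
|---|---|
| 0.3 | 67.7% |
| 0.5 | 69.7% |
| 0.7 | 72.2% |
| 0.8 | 73.8% |

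**Step 3: what it would cost to keep two primary tests, either sufficient, at a controlled 5%.** With Bonferroni (0.025 each), n per arm = 2 × (2.241 + 0.842)² × 6.25 = 118.8, rounded up to 119. That is 238 completers and 238 / 0.80 = 297.5, so 298 enrolled. Staying at 100 per arm gives Φ(2.83 − 2.24) = 72% power at each time point.

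**The case against.** The strongest reply is that the article as a whole points to one primary comparison. The Abstract and the Outcomes section are explicit, the sample size is built on a single test, and the Statistical analyses section names post-intervention MVPA scores as the dependent variable. On that view the Hypothesis sentence is the outlier, and a claim of primary success from 6 months alone would contradict the declared primary outcome. This stands, and it shows which way to reconcile the text. It does not remove the conflict, because no sentence says which section governs. An unseen analysis plan might set an order, but these published sentences would still disagree.

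A reader might go further and infer that the plan lets success be declared from either time point at a type I error of 8% to 9%. The documents do not support that as a flat statement:

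- No either/or rule is written. The Hypothesis section joins the time points with *and*, which can equally be read as requiring both.
- A figure between 8% and 9% needs a correlation of roughly 0.53 to 0.77, which the article does not supply.
- It is a two-sided rate that also counts false findings against the intervention. In the hypothesised direction the comparison is about 3.9% to 4.5% against 2.5%.

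A reader might also extend the point to the secondary outcomes and the three-way interactions, since the same 0.05 rule covers them. That does not follow. The outcomes are labelled secondary and the interactions are presented as moderator analyses. Whether to adjust them is commonly left to the analysis plan. Any count of such tests would also have to assume how the 20 attitude statements are scored.

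**Conclusion.** The contradiction is real and concerns the trial's confirmatory claim: two time points are primary under Hypothesis, one under Outcomes and measures, with sample size and significance rule written as if the question did not arise. Only the 3-month-only reading keeps both stated operating characteristics.

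Under the either-time-point reading, which the text permits but does not state, the two-sided error is above 5% and at most 9.75%; the 9.1% to 7.8% range rests on an assumed correlation of 0.5 to 0.8. Under the both-required reading the error is controlled and the loss is in power, to about 68% to 74% for an assumed correlation of 0.3 to 0.8 and 10 minutes at both times. The sample size calculation itself is sound. The defect is a correctable inconsistency and does not invalidate the design or the 3-month test.

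**What to change.** Three wording changes, made before outcome data are compared by arm:

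1. **Hypothesis:** state that the sole primary hypothesis is a group difference in MVPA at 3 months, and move the 6-month statement to the secondary hypotheses.
2. **Outcomes and measures:** add MVPA at 6 months to the secondary outcomes.
3. **Statistical analyses:** state that 6-month MVPA is tested at two-sided 0.05 as a confirmatory claim only if the 3-month test is significant; otherwise it is reported as an estimate with its 95% confidence interval.

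The fixed sequence uses no extra alpha, so 200 completers, 250 enrolled and the 3-month power are unchanged. The one cost is that a 6-month result on its own could no longer be claimed as confirming the primary hypothesis.

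If the investigators want both time points to remain primary, they must say whether either or both must succeed and accept the corresponding loss of power. The alternative of enrolling 298 with a Bonferroni split is hardly open, since Trial status plans recruitment to end in April 2018, before the article appeared in July 2018. No adjustment of the other secondary outcomes or the interactions is asked for here.

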## Methods

### Study design

SCAMPI is a two-arm parallel randomised controlled trial (RCT) (1:1 ratio) conducted in Stockholm County, Sweden, with assessments at baseline, post intervention at 3 months and 6 months post randomisation (see Fig. 1 for study outline). This study protocol follows the SPIRIT 2013 statement [21, 22] and the intervention is described according to the CONSORT – EHEALTH checklist [23].

**Fig. 1 Fig1:**
[figure not shown]
Flow-chart of the SCAMPI trial design

### Participants and recruitment

Participants are recruited from a random sample of 5000 adults (aged 20–65 years) living in Stockholm County drawn from the population register at Statistics Sweden. Eligible participants are 20–65 years old, able to understand Swedish well enough to fully understand the study aims and consent to participate, and have access to a smartphone. Those who are unable to perform MVPA (i.e. brisk walking or cycling) will be excluded.

Potential participants are sent an inquiry letter by Statistics Sweden to their home address providing them with written information about the study. Participants register their interest via the study website, send in a response letter by post or contact the research group directly by email or telephone. Those who do not respond to the inquiry letter (including the two reminders after 2 and 4 weeks, respectively) will remain anonymous to the research team. Once informed consent is obtained, baseline measures are collected. Participants are asked to fill in a web-based questionnaire with questions regarding perceived neighbourhood walkability, attitudes towards active transportation, health related quality of life, self-reported physical activity level and socio-demographic data. Thereafter, participants are asked to wear an accelerometer to measure physical activity for seven consecutive days. Participants are also asked to download an app free of charge on to their smartphone, TRavelVU (Trivector AB ©), which passively captures travel behaviour for the same seven days as the accelerometer is worn. The app is compatible with both iOS (version 8.4 or higher) and Android (version 4.4 or higher) smartphones.

### Randomisation and blinding

Upon completion of baseline measures, participants are randomised to the intervention or the control group in a 1:1 ratio. A computer-generated random allocation sequence list (in blocks of two) is generated in Stata 13 (StataCorp LP, College Station, Texas, USA). To ensure allocation concealment to study personnel until group allocation, the allocation list is monitored by a member of the research group with no participant contact. After randomisation, participants receive an email containing information about their group allocation. Assessors of the primary and secondary outcomes are blinded to group allocation; however, due to the design of the study participants are not blinded to their allocation.

### Control group

The control group participants are encouraged to continue with their normal routines and to monitor their daily travels in the TRavelVU app. The app passively collects data on the mode of travel, duration and speed for 6 months, but no behaviour change content is provided. Upon completion of the trial, participants from the control group will have access to TRavelVU Plus, see below, if they wish to.

### Intervention

#### Overall

The overall aim of the SCAMPI intervention is to increase physical activity levels by promoting active transport. Once allocated to the intervention group, participants receive an email with a user manual for the TRavelVU Plus app. This app differs from the TRavelVU app as it includes a 3-month behaviour change program promoting active transportation. Features of the TRavelVU Plus app (i.e., messages (sent as push notifications), goal setting and feedback functions) are activated and start with a welcome message. The message includes a goalsetting function where participants set their first weekly goal for active transportation, for example 5 h. As guidance, they are informed of the recommendations for adults of 150 min of MVPA per week, but are encouraged to set a goal based on their current activity level. Feedback on the goal is provided in different formats during the week. At the end of the week, participants are able to adjust their goal for the following week. After 3 months, the features of TRavelVU Plus disappear; however, participants are encouraged to keep registering their travels in the TRavelVU app until after the 6-month follow-up assessment.

#### Development and content

##### The TRAvelVU app

TRavelVU, an automatised and objective assessment of travel behaviour was developed by Trivector AB ©, a company with expertise in sustainable and active transportation. Once downloaded, the TRavelVU app continuously and passively (without manual input) collects data in real time on location and travel speed (GPS). When the user is in motion, the app starts to send GPS data to the server, and these data are transferred into speed and acceleration profiles. The analysed data are then immediately sent back to the app where participants can view their journey (distance, route and suggested mode of transport). The users enter data about their destinations in the app and edit modes of transportation and start/stop times of trips if these have been registered incorrectly. Once a location has been added to the app by the user (e.g., “home” or “office”), TRavelVU remembers this and automatically suggests this destination for future trips. Algorithms are based on a fuzzy logic approach on a number of different variables (e.g., mean speed and percentile speed), to identify the most likely modes of transportation for trip segments [24, 25]. The app has been developed with the aim of minimising battery consumption. All participant data are anonymous and linked to a unique identification number. Using these data, TRavelVU provides detailed information on the participant’s travel behaviour. Fig. 2 shows a screenshot of a daily summary of travel modes for a user in TRavelVU.

